**5. Intervention**

***5.1 EPIC WheelS Program (experimental group)***

EPIC WheelS is a customized program combining 2 structured 1-hour sessions with an expert Trainer and 4 weeks of self-paced practice and training at home. Study Trainers will be occupational therapists with ≥ 5 years of clinical experience in wheelchair provision/training, and will have received a 2-day comprehensive orientation to the EPIC Wheels program from [name]. Subjects will attend an initial assessment/training session and receive a customized home program from their Trainer. The home program is delivered using a portable, interactive *computer tablet* that can be used for practice in their home or other community venues. After 2 weeks of practice, subjects return for a second 1-hour training session. The Trainer updates their program and they continue practicing at home for another 2 weeks. To promote adherence and safety, subjects will have a caregiver attend all training sessions and supervise their home training. The tablet collects data on *all user activity* (i.e., each touch-stroke is time-stamped), downloading usage data to the Trainer over the Internet. Trainers monitor subject activity remotely and will contact subjects by telephone at the end of weeks 1 and 3 to promote program adherence.

***5.2 Control Group***

To provide a comparable level of investigator attention, control group subjects will receive two 1-hour social visits. To control for Trainer bias, the experimental and control groups will have separate Trainers. During social visits, the Trainer will discuss subjects’ current community activities and their experience using the wheelchair, and provide verbal information related to barriers encountered (see Appendix N). Subjects will receive a computer tablet with cognitive stimulation games to account for activity and tablet device exposure. To minimize attrition, control subjects will receive a DVD with a condensed MWC skills education program after the post-intervention data collection is complete.

***5.3*** ***Usual Care (both groups)***. Both control and experimental group subjects will have received usual care for MWC mobility training during the acquisition of their wheelchair. Typical care in Canada varies between and within regions, but is typically limited to ≤ 30 minutes of training, focusing primarily on transferring from the wheelchair to the tub, toilet and bed to expedite discharge home.

**6. Training and equipment**

**6.1 Program details**

[figure not shown]
The EPIC WheelS program includes a comprehensive, structured library of educational material and training activities, organized in a hierarchy from simple to complex. Following the initial assessment and training session, Trainers will select a sub-set of skills and training activities to incorporate into a subjects’ home training program based on ability, safety, and relevance. Trainers monitor a subject’s progress through on-line access to tablet usage data and re-assessment during the second training session (@ 2 weeks), releasing more advanced skills and activities at any time via the Internet. The illustration here is an example of an individualized program, where the Trainer releases a series of skills from the EPIC WheelS library over time (Safety > Propulsion > Negotiating obstacles > Popping casters), while selectively hiding 2 skills that are not relevant for this subject.

The *home program component* is delivered using a 10” portable computer tablet (i.e. Motorola Xoom^TM^). The tablet is menu driven and interactive, using a touch-screen interface. A tablet offers considerable advantages over traditional paper/hand-out home programs. Training is provided in a multi-modal format with illustrations and videos, allowing detailed step-by-step guidance, close-ups, and demonstrations using age-appropriate older adult models. Practice activities can be clearly demonstrated (to ensure they are performed appropriately) and include imitative, function-based, and interactive game-related activities. A built-in camera enables subjects to video record their performance, which they can review for accuracy or forward to their Trainer for feedback. Subjects can also send text or voice emails to their Trainer using the tablet; Trainers will review and respond to emails within 48 hours. The tablet is housed in a rigid case with a simple strap that wraps around the wheelchair armrests. Subjects can secure the tablet on their lap and practice anywhere in their home or community, or place the tablet on another surface for viewing or video recording. Training activities are highlighted after completion, indicating to the subject they can advance to the next component. A “Progress” tab provides regular updates on the number of training sessions and minutes practiced each day, and “reward” icons are produced for meeting practice parameters to reinforce adherence. The tablet will have Internet access for email and data transfer/update capability, but the training program can operate in stand-alone mode as well. For the purposes of this study, the tablet will operate as a single-function device (i.e., other tablet applications and functions like web browsing/downloading will be disabled).

Maximizing training frequency and practice in the natural context of use are essential elements for rehabilitation home programs targeting motor skills in older adults. A 2010 Cochrane review of exercise adherence identified programs incorporating self-efficacy strategies, clinician monitoring, and progressive challenges are more effective in improving adherence, frequency, and duration of exercise.^33^ EPIC WheelS integrates principles from Social Cognitive theory^34, 56^ and strategies from Andragogy (adult learning) theory^57, 58^ as active ingredients to optimize adherence and skill acquisition. The program is individualized and progress is monitored by an expert Trainer. Skills are sequenced from simple to complex, and practice includes activities designed for a home setting. Since programs for older adults are more well-received when they focus on user-identified outcomes,^33, 59^ activities identified by the WhOM are incorporated into subjects’ programs.

The use of a computer tablet to deliver the home training program offers advantages of portability, audio-visual versatility, flexible configuration and real-time updating. Although older adults are less likely than younger people to embrace technologies such as a computer, their use of computers continues to grow. 2006 and 2010 studies in the United States found 84% of those over 60 years had experience with computers^60^ and 40% of those over 65 years are regular computer and Internet users.^61^ Use of a tablet involves some new learning, and age-related declines in memory and fluid intelligence may restrict uptake. These issues are addressed through self-paced training, structures for success experiences to build confidence, and by adapting the interface for familiarity and ease of use with minimal memory requirements.^62, 63^ Consumer, caregiver and clinician input was incorporated during EPIC WheelS program development to ensure the delivery format addresses these concerns.

**6.2 Experimental group (EPIC WheelS)**:

***6.2.1 Training Session 1.*** The Trainer will conduct the initial 1-hour session at a rehabilitation centre, following a Protocol Binder and Training Checklist (Appendix O). The training regime follows a structured sequence of skills of increasing complexity. After training, they will provide the subject and caregiver with a 30-minute orientation to the home program and tablet (including a written handbook for reference) and provide an internet-enabled tablet with the EPIC WheelS program. Subjects will be strongly encouraged to have their caregiver supervise home practice; the tablet will *prompt subjects to acknowledge review of the safety information* when performing activities with a risk for tips and falls before they can proceed. The American College of Sports Medicine best practice guidelines for older adults recommend that during physical activity, exertion remain in the moderate range and advocate use of the Borg Perceived Rate of Exertion (PRE) scale (see Appendix P).^64^ The PRE scale is rated from 6-20 with “somewhat hard” falling in the interval of 12-14.^65^ The Trainer will review the Borg PRE and guidelines for not exceeding moderate exertion during training.

***6.2.2 Home Program component***. The home program is individualized for subjects and activities are progressed by the Trainer via Internet updates to provide seamless access. A training schedule will target a minimum of 1-2 sessions/day, 15-30 minutes in length, at least 5 days per week. These guidelines are based on the National Blueprint consensus document on promoting physical activity for adults over 50 years, which advocates that lifestyle- or endurance-related activity of moderate intensity should be undertaken for at least 30 minutes (in bouts of at least 10 minutes) 5-7 days per week.^64^ Adherence with this schedule is achievable, as demonstrated by a study of home-based training program for improving hand function among stroke survivors (*n* = 77; *m* = 57 years) which obtaining 96% compliance for 1.3 hours of training per day, 7 days per week over 5 weeks.^66^ The minimum training time with EPIC WheelS (Trainer @ 2 hours + home program @ 6 hours = 8 hours) is at least comparable to 1:1 training time in other clinical studies using the WSTP.

**7. Safety**: The EPIC WheelS program incorporates extensive *safety-related material*, including teaching the safest mobility strategies; use of safety equipment; recognizing unsafe situations; and seeking assistance when skills are insufficient to address environmental barriers. At the initial training session, subjects are provided with protective wheeling gloves and a Spotter’s strap for safety. Caregivers will be invited to attend and participate in both training sessions, and subjects will be strongly encouraged to have a caregiver supervise all home training activities. Operating a wheelchair in the community carries innate risks that cannot be entirely eliminated. However, for the experimental group subjects, EPIC WheelS offers education and training designed to minimize risks of wheelchair operation. *This knowledge should reduce the risk of a fall or injury that they might be exposed to in their everyday use of a MWC had they not received this program*.

Any unsafe performance observed during training will be addressed immediately with corrective feedback. Subjects will be encouraged to contact the Study Coordinator immediately if they experience unusual discomfort, pain or physical symptoms. A Data and Safety Monitoring Board (DSMB) will review accumulating outcome data and advise the investigators regarding safety issues, evidence of benefit, and need for modification to the study design.^67^ The DSMB will include 4 members external to the research team: a statistician, a physiatrist, a clinician (OT/PT), and a MWC user. Adverse events will be documented by the study Trainer using the Treatment Protocol Checklist and will be reported to the DSMB as well as the applicable Ethics Review Board(s).

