*Inclusion criteria*. Subjects will be ≥ 55 years old; live in the community within the metropolitan boundaries; self-propel a MWC ≥ 1 hour/day; use their MWC for mobility outside the home; have used a MWC for < 1 year; have a caregiver able to attend training sessions and supervise home training.

*Exclusion criteria*. Individuals will be excluded if they cannot communicate and complete study questionnaires in English; anticipate a health condition or procedure that contraindicates training (e.g., surgery scheduled which would impair physical activity); currently receive out-patient therapy that includes wheelchair mobility training; or if they exclusively foot propel their wheelchair.

**4. Outcome measures.** Wheelchair device characteristics will be collected using the Wheelchair Specification Form (see Appendix A). Descriptive characteristics including age, sex, marital status, highest level of education, primary diagnosis related to MWC use, length of time using the MWC, and propulsion method will be collected along with cognitive status measured using the Standardized Mini-Mental Status Exam (Appendix R). Handgrip strength has been demonstrated to be an accurate surrogate measure of overall strength^36^ and will be measured using a Jaymar^TM^ 5030J1 dynamometer.

**4.1 Feasibility outcomes** for process, resources, management, and treatment parameters will be measured during study administration and at study’s end. *Process* outcomes will include recruitment, consent and retention rates at each site. The Post-treatment Participant Questionnaire and follow-up interviews will be used to evaluate perceived benefit. *Resource* outcomes will be monitored by tracking study staff time logs and tablet usage data. *Management* issues will be evaluated using the trainer Evaluation Form and by tablet reliability/loss data. *Treatment* outcomes will include reporting of adverse events and statistical analysis of the treatment effect.

**4.2 Clinical outcomes** will be measured at baseline and post-treatment (1 month).

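### Section 5.1 says a caregiver will supervise home training, sections 6.2.1 and 7 only encourage it, and no supplied text requires anyone to be present for activities flagged for tip or fall risk

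*Combined protocol and SAP*

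**What the plan says.** Four places in the combined protocol and SAP describe the caregiver's role.

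- **Inclusion criteria (Methods, section 3).** Each subject must "have a caregiver able to attend training sessions and supervise home training".
- **Section 5.1.** In the interest of adherence and safety, "subjects will have a caregiver attend all training sessions and supervise their home training".
- **Section 6.2.1.** After the first session the Trainers take both people through the program: "they will provide the subject and caregiver with a 30-minute orientation to the home program and tablet". For practice at home, however, "Subjects will be strongly encouraged to have their caregiver supervise home practice". The tablet also asks subjects to acknowledge that they have reviewed the safety information "when performing activities with a risk for tips and falls before they can proceed".
- **Section 7 (Safety).** On the sessions, the text reads "Caregivers will be invited to attend and participate in both training sessions". On practice at home, it reads "subjects will be strongly encouraged to have a caregiver supervise all home training activities".

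The plan describes other safeguards. Trainers choose skills partly for ability and safety, re-assess at two weeks and control the release of harder skills (section 6.1). Remote oversight continues between sessions: "Trainers monitor subject activity remotely and will contact subjects by telephone at the end of weeks 1 and 3". Subjects can send video to the Trainer for feedback (section 6.1). Section 7 adds safety teaching, gloves, a Spotter's strap and a DSMB.

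**The concern.** The protocol sets two different rules for the same two things, attendance at the sessions and supervision at home. The weaker rule is the one in the Safety section. The difference matters most for the activities that the program itself singles out as carrying a risk of tipping or falling. The Background (item 2) describes tips and falls as frequent in manual wheelchair users and a common cause of injury. The subjects here are 55 or older, with less than a year of wheelchair use.

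Two things are at stake. The first is subject safety during practice with no Trainer in the room. The second is how the safety result can be read. Safety is among the primary feasibility objectives, and the feasibility results decide whether the protocol goes forward largely unchanged (section 8.1). If a subject falls at home, no supplied text provides for recording whether a caregiver was there. It would then be hard to tell a problem with the program from a lapse in supervision.

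**Working it through.** The point concerns wording, and the plan gives no figure to reproduce. The check compares every supplied statement on caregiver attendance, caregiver supervision and the tablet safety prompt.

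| Place | Attendance at the two sessions | Supervision at home | Force |
|---|---|---|---|
| Inclusion criteria | able to attend | able to supervise | condition of entry |
| Section 5.1 | will attend | will supervise | declarative |
| Section 6.2.1 | caregiver included in the orientation after session 1 | strongly encouraged | advisory |
| Section 7 | invited | strongly encouraged | advisory |

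**Step 1: do the sections agree?** They do not. On attendance, section 5.1 is declarative and section 7 is an invitation. On supervision, section 5.1 is declarative and sections 6.2.1 and 7 are advisory. The current text differs on both points.

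**Step 2: does the inclusion criterion settle it?** It does not. It secures a caregiver who is able to supervise at the time of enrolment. It does not say that the caregiver is present when practice takes place.

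**Step 3: what happens when a flagged activity starts?** Section 6.2.1 describes one step: the subject acknowledges the safety information and can then go on. No confirmation by or about a caregiver is mentioned.

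**Step 4: do the other safeguards supply a second person?** Skill selection and release act before practice. Remote monitoring, the telephone calls and video review act after it or at a distance. Section 7 provides for immediate correction of unsafe performance that is observed in training, but the Trainer is not at the home sessions. The Spotter's strap, by its name, anticipates a spotter, yet no supplied text says that one must be there.

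**Step 5: can section 5.1 alone close the gap?** Read as binding, its general wording would cover flagged activities too. It does not name them and states no check, and the two later sections soften it.

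**Step 6: can a size be given?** The documents do not say how much practice is flagged, how often a caregiver would be absent, or what the fall risk is during training with or without one. No effect on falls can be calculated.

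**The case against.** The strongest reply is that the sections can be read together. The inclusion criterion secures an able caregiver, section 5.1 describes the intended delivery, and sections 6.2.1 and 7 state what staff can realistically achieve in a private home, where they cannot compel anyone to be present. Subjects already propel themselves for at least an hour a day and go outside the home, and section 6.1 treats frequent practice as essential. Encouragement combined with Trainer-controlled release is then a defensible balance. Trainers also share a 2-day orientation (section 5.1) and a Protocol Binder and checklist (section 6.2.1), so different practice at the two sites is not a given.

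Much of this stands. It explains why supervision might be worded more softly in one place than another. It explains less well why attendance at a session on study premises is definite in one section and by invitation in another. It also does not say what applies when encouragement fails for an activity that the program has itself marked as risky. The Binder, Appendix O, the handbook and the tablet's own safety text were not supplied. A stricter rule may exist there, but the three sections would still disagree.

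The reply is also right about scale. The only rate in the documents is a yearly tip or fall incidence of 5.2% (Background, item 2). For 20 subjects over one month this gives 20 × 0.052 / 12 = 0.087, or about 0.09 events. That rate describes wheelchair use in general, not skills training, so it neither shows a large problem nor excludes one.

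**Conclusion.** The inconsistency is real and should be corrected. Under sections 6.2.1 and 7, a novice older user may carry out a tip- or fall-risk activity alone after acknowledging a prompt; section 5.1 says a caregiver supervises. Confidence is medium, because the conclusion rests on the supplied text and the operational documents might already contain a rule. The size of any effect on falls is unknown.

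A reader might infer more than the documents support:

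- **That most training is unsupervised risky practice.** Section 6.2.2 puts 6 of the 8 minimum hours at home (6 / 8 = 75%). This counts all home practice, whether flagged or not and supervised or not, so it does not measure the gap.
- **That subjects are left without protection.** The safeguards in sections 5.1, 6.1 and 7 are substantial. What is missing is a stated requirement that someone be present at a specific moment.
- **That the two sites will apply different rules.** The wording permits it, but the shared orientation and Binder may prevent it.
- **That the adherence evaluation is compromised.** Section 8 bases it on training time and session counts from the tablet, and these do not depend on who was present.

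**What to change.** Align sections 5.1, 6.2.1 and 7 on one rule:

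1. The caregiver attends the training sessions, as section 5.1 already says.
2. A caregiver must be present for any activity that the tablet flags for tip or fall risk.
3. Supervision of other home practice is strongly encouraged.

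Add a caregiver-present confirmation to the existing tablet safety prompt. Section 5.1 says the tablet time-stamps every touch, so the answer would be logged and could be read alongside any adverse event. If the Protocol Binder, Appendix O or the handbook already sets such a rule, carry that rule into the three sections instead of writing a new one.

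The cost is wording in three sections and one line on a prompt that already exists. Eligibility does not change, since an able caregiver is already required, and no extra visits are needed. There are two drawbacks. Some flagged practice may wait until a caregiver is available, while unflagged practice stays self-paced. The confirmation is self-report, so it states the rule and leaves a record but does not prove that anyone was there. The sponsor could choose a different rule; the essential thing is that one rule is stated throughout and that it covers flagged activities explicitly.

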**OBJECTIVES**

**Primary Objectives: Feasibility Outcomes**

To assess the feasibility of study methods and procedures for a subsequent large-scale RCT, including:

1. *Process issues* of subject recruitment, consent, retention, and perceived benefit;
2. *Resource issues* of treatment adherence, burden of data collection, incorporating a health utility index, and intervention burden;
3. *Management issues* of equipment reliability, subject processing, and protocol administration; and
4. *Treatment issues* of safety, response, and treatment effect.

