**Methods**

**
[figure not shown]
1. Research Design.** This 2-year feasibility study will use a two-site (Winnipeg and Vancouver) randomized controlled trial to compare differences in older adults’ wheelchair mobility skills with EPIC WheelS versus usual care. Subjects will be randomly assigned to the experimental group (usual care + EPIC WheelS) or a control group (usual care only) using a 1:1 allocation ratio between groups. To support balance between groups and masking of assignment, a central computerized randomization process will be designed by our team statistician ([name]), with an undisclosed block size and stratified by site (Winnipeg *n* = 20; Vancouver *n* = 20). Once subjects are enrolled, the Study Tester will collect baseline data and enter them into a secure database. The Site Coordinator will contact [name] via telephone or email and obtain group assignment within 48 hours. Subject contact information will be forwarded to the appropriate group Trainer to arrange for an initial training session or social visit. To address bias, subjects will be instructed not to discuss their program and Study Testers will be blinded to group allocation.

Experimental group subjects will attend 2 training sessions with an expert Trainer. The Trainer will individualize a structured home training program, delivered via a computer tablet, and subjects will train for 1 month. The Trainer will make telephone contact at the end of weeks 1 and 3. Control group subjects will receive 2 social visits to address attention balance through exposure to study personnel. In addition, they will be provided with a similar computer tablet with cognitive training games to account for tablet device and activity exposure.

**2. Assessments.** The clinical outcome measures will be collected at baseline (pre-randomization) and post-intervention. A 1-month intervention will provide ≥ 8 hours of training, which is comparable to clinical studies using the WSTP where a significant improvement in skill capacity was observed.^17-19^

**3. Subjects.** A total of 40 community-dwelling MWC users living in Winnipeg and Vancouver (20 at each site) will be recruited on a volunteer basis (see Section 8.1 for sample size justification). To optimize the impact of the treatment, individuals with less than one year of MWC use will be recruited as they are still developing routines and patterns of wheelchair use and potentially more amenable to adapting their mobility techniques.^12^

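### Adverse events are recorded by arm-specific Trainers with unequal scheduled contact and no common enquiry, so counts by arm are open to ascertainment bias

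*Combined protocol and SAP*

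**What the plan says.** **Who records.** Section 7 (Safety): "Adverse events will be documented by the study Trainer using the Treatment Protocol Checklist". The events then go to the DSMB and the ethics boards. Section 5.2 gives the two arms separate Trainers. Section 1 of the Methods blinds the Study Testers, and no blinding of Trainers is described. The same safety section encourages subjects, without restriction by arm, to contact the Study Coordinator about unusual symptoms.

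**Contact in the experimental arm.** Methods, section 1: "Experimental group subjects will attend 2 training sessions with an expert Trainer". Section 5.1 places the second session after two weeks of practice and adds: "Trainers monitor subject activity remotely and will contact subjects by telephone at the end of weeks 1 and 3 to promote program adherence". Section 6.1: "Subjects can also send text or voice emails to their Trainer using the tablet; Trainers will review and respond to emails within 48 hours".

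**Contact in the control arm.** Section 5.2: "To provide a comparable level of investigator attention, control group subjects will receive two 1-hour social visits". Neither visit is dated. No calls, Trainer e-mail or usage monitoring are described for controls.

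**How the data are used.** The primary feasibility objectives include treatment issues "of safety, response, and treatment effect". Section 4.1 lists adverse event reporting among the treatment outcomes. Section 8 summarises outcome variables for groups, with frequencies and proportions for categorical ones.

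**The concern.** An adverse event enters the record when a Trainer learns of it, and the number of scheduled occasions for that differs by arm. With equal true rates, the arm that is contacted more often can show more recorded falls, pain or minor injury. The recorder also knows which programme the subject is on.

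Safety is part of a primary feasibility objective, and the DSMB advises on it. Section 7 itself expects that the training should lower the risk of falls and injury. Readers are therefore likely to set the two arms' counts side by side whether or not a test is planned. In a trial of 40, one or two events captured in one arm and missed in the other could change that reading and carry into the design of the larger trial.

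**Working it through.** The plan gives no figure for adverse event capture, so there is none to reproduce. The sample size does not depend on this point.

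**1. Scheduled Trainer contacts**

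| | Experimental | Control |
|---|---|---|
| Face-to-face | 2 sessions | 2 social visits |
| Telephone | 2 calls (end of weeks 1 and 3) | none described |
| Total scheduled | 4 | 2 |
| E-mail to Trainer, usage monitoring | yes | none described |

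The experimental arm also has a "30-minute orientation to the home program and tablet" (section 6.2.1). Controls receive a tablet too, but whether they have an orientation is not stated, so I do not count it.

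**2. Capture if every scheduled contact can elicit an event.** Let q be the probability that one contact elicits an event. This is an assumption; the documents give no value. With k independent contacts, capture = 1 − (1 − q)^k.

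| q | Experimental, k = 4 | Control, k = 2 | Ratio |
|---|---|---|---|
| 0.3 | 1 − 0.7^4 = 76% | 1 − 0.7^2 = 51% | 1.49 |
| 0.5 | 1 − 0.5^4 = 94% | 1 − 0.5^2 = 75% | 1.25 |
| 0.7 | 1 − 0.3^4 = 99% | 1 − 0.3^2 = 91% | 1.09 |

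With equal contacts the ratio is 1.00 at any q.

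**3. Sensitivity to timing.** The first contact starts the programme and cannot capture later events. Assume events spread evenly over four weeks, and experimental contacts at the end of weeks 1, 2 and 3. Events in weeks 1 to 4 are then followed by 3, 2, 1 and 0 contacts. Experimental capture = [(1 − (1 − q)^3) + (1 − (1 − q)^2) + q + 0]/4; at q = 0.5 this is (0.875 + 0.75 + 0.5 + 0)/4 = 53%. Control capture is q/2 if the second visit is at the end of week 2, and q if it is at the end of week 4.

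| q | Experimental | Control, week 2 | Ratio | Control, week 4 | Ratio |
|---|---|---|---|---|---|
| 0.3 | 37% | 15% | 2.4 | 30% | 1.2 |
| 0.5 | 53% | 25% | 2.1 | 50% | 1.1 |
| 0.7 | 65% | 35% | 1.8 | 70% | 0.9 |

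Size, and even direction, turn on a control visit date that the plan does not give.

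**4. Scale in events.** The Background gives a yearly tip/fall incidence of 5.2%. At constant risk the monthly figure is 1 − (1 − 0.052)^(1/12) = 0.44%. That is 20 × 0.0044 = 0.09 expected per arm, and a 1 − (1 − 0.0044)^40 = 16% chance of any among 40 subjects. If the true monthly risk of any recordable event were higher, say an assumed 20% in both arms, then at q = 0.3 the step 2 model gives 20 × 0.20 × 0.76 = 3.0 recorded events against 20 × 0.20 × 0.51 = 2.0.

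**The case against.** A reader might infer that a planned safety comparison is biased. The documents do not support that. No between-arm analysis of adverse events is specified. The named safety contrast is the WST Skill Safety score, analysed by ANCOVA (section 8.2.2); that is a scored test in a trial with blinded Testers, and Trainer-recorded events do not enter it. What remains is that section 8 summarises outcomes by group and the DSMB reviews safety, so an informal comparison is likely.

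A reader might also infer that week-4 events in both arms surface only if volunteered. For controls this cannot be said, because their visits are undated. All subjects have a post-treatment assessment and a participant questionnaire (section 4.1). The questionnaire is described only for perceived benefit, but its content is not available for review. What stands is narrower: no scheduled Trainer contact follows week 3 in the experimental arm, and no adverse event enquiry is described at the post-treatment visit.

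The Study Coordinator route is open to both arms, so control events have an outlet. It depends on subjects volunteering, however, and does not equalise contact with the person who records events.

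The calls exist to promote adherence and are part of the intervention, so they may elicit few events. Leaving them out of the control arm is a defensible choice, and two 1-hour visits do mirror two 1-hour sessions. This stands. The comparable-attention statement is fair for visits but not for total contact.

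Appendices D, N and O are not available and may describe control procedures or use of the checklist in controls. Even so, the main text should state how adverse events are sought in each arm.

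**Conclusion.** The concern holds as a gap in ascertainment, not as a demonstrated bias. As written, adverse events are recorded by an arm-specific Trainer who knows the allocation, scheduled contacts are 4 against 2, and no common enquiry is described. Counts by arm are therefore open to ascertainment bias.

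No single distortion figure should be quoted as a finding. Ratios of about 1.5 to 1.1 follow from q of 0.3 to 0.7 when every contact counts. The timing variants run from 2.4 to 0.9. All of them assume equal true risk and that adherence calls and social visits elicit events equally well, and the documents establish neither. With few events expected, the absolute effect may be only an event or so.

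The primary WST analysis and the sample size are unaffected. This is a modest, inexpensive improvement.

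**What to change.** - At the existing post-treatment visit, after blinded testing is finished, give every subject in both arms the same short form on falls, injury and pain covering the whole month. Make it self-completed or strictly scripted: the Site Coordinator obtains the allocation (Methods, section 1), so free questioning by that role would not be blind. Placing it after testing protects the Testers' blinding.
- Base any by-arm adverse event table, including tables for the DSMB, on this form. List Trainer-recorded and volunteered events separately, by source. Immediate reporting to the DSMB and ethics boards continues as planned.
- State the dates of the control visits and whether the Treatment Protocol Checklist is used in both arms.
- Limit the comparable-attention statement in section 5.2 to face-to-face visits. Matching calls in the control arm are optional: 2 × 20 = 40 short calls, at the price of more attention to controls.

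The cost of the main change is one short form per subject (40 in all) and some recall error over a month.
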